#### Procedure and data management

A two-stage screening process will be used to select participants (timepoint T-1; Table 1). Initial contact will be made by phone by research team members with expertise in recruitment. At this stage, only participants who report no major physical, medical, or sensory limitations will be invited to come to the laboratory for further investigation. During the on-site visit, participants will be presented with the information and consent form. In Switzerland, participants will be offered to receive the information and consent form prior to their visit. Once they sign the consent form, inclusion and exclusion entry criteria will be measured for the second-stage screening. The Fried’s phenotype scale [2] will be used to exclude frail individuals and to determine frailty level among other participants who will be identified as either robust (score of 0) or pre-frail (score of 1 or 2). In addition, the participant’s technology (e.g., use of tablet, email, social network) and gaming profile will be established with an ad-hoc questionnaire. Eligible participants will receive an ID number. All data will be anonymized and maintained in REDCap, a secure online database [47]. Access to data will be restricted by type of data (e.g., assessors will only have access to assessment data). Furthermore, data collected directly by the programme will be transmitted and maintained in a secured server located at the Haute École Spécialisée de Suisse Occidentale (HES-SO).

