#### Randomisation and blinding procedure

A randomisation list will be generated in Switzerland, independently from the research project and implemented using REDCap. In each site, a team member not involved in assessment or monitoring will assign participants by pressing a “randomisation” button on REDCap. A stratification will be done according to the frailty status. Within each stratum (robust and pre-frail), participants will be assigned to one of the two conditions (StayFitLonger or active control) according to separate randomisation schedules with a 1:1 ratio. Couples (e.g., married individuals) who participate in the study will be assigned to one of the two conditions as a pair: the first member of the couple will be randomised, and the second will be assigned to the same intervention. This has been implemented to avoid contamination in cases where two individuals living in the same household would be randomized to different training programmes.

Assessors will be blind to the hypotheses and to participants’ assignment, as they will only have access to the testing sessions. Participants will be asked not to discuss their training programme with assessors. If such a circumstance were to occur, it will be reported but should have minimal effect on data integrity, as assessors will be blinded to the hypotheses. Research team members responsible for the statistical analyses will be blind to the training conditions. Study coordinators and instructors involved in the introductory courses and supervision of home-based training will not be blind. Participants will be aware that the trial has two different training conditions and that they will be randomly allocated to one of them. However, they will not be informed of the study hypotheses and therefore will not know which one is the experimental condition. Both programmes will have a similar main screen layout and name, and the wording of the recruitment documents and consent forms will not convey the notion that one condition is hypothesised as inferior in terms of its effects on physical capacities and cognition [48].

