There will be four cognitive training activities which target problem solving, semantic memory, prospective memory, and divided attention. The *Quiz* activity will teach different strategies [49, 50] to learn new vocabulary and semantic repertoires (e.g., mushrooms, trees, flowers, dogs, etc.; Fig. 1c). Participants will choose first a repertoire of interest and will be asked to perform word-image associations related to the repertoire. Based on their level of proficiency in the selected repertoire, participants will then be offered different learning techniques: *completing* (relying on cues for help) or *copying/completing* (copying the word while using pure errorless learning and then completing while using encoding cues). Participants will continue to explore the repertoire through practice using an optimal number of cues to obtain the best performance while limiting the production of errors. This practice will be completed once participants reach at least 60% of correct responses without cues. Then, participants will be invited to a final evaluation without any help. Feedback will be provided with the option of continuing training using the repertoire or choosing another one. The *4 Images/1 Word* activity will train cognitive flexibility (Fig. 1d). Participants will be shown four images that are associated with an overarching concept and will be asked to find and write down the associated concept. Two types of cues will be provided to help them solve the task: number of letters in the target and some of the target letters mixed with distractors. The *Attention!* activity will train participants to vary their attentional priority in dual-tasks [40] while exploring a city on a two-wheel vehicle (Fig. 1e). The dual-task will involve detecting different targets in the environment (i.e., people, 4-wheel vehicles or buildings) by pressing a button on the screen (task A), and at the same time detecting sewer covers with foot taping (task B). The foot response will be recorded by a motion sensor attached to the waist or shoe. The activity will comprise 30 levels with a progressive increase in the degree of difficulty. Difficulty will be increased by manipulating the number of targets, the number of distractors and the speed of the vehicle driven by the player (i.e., bicycle, scooter, motorcycle) and by introducing a response contingency condition (if/then). Participants will complete first each task (detection of targets in the environment and detection of sewer covers) in focused attention. They will then be asked to combine the tasks with different priority levels during a series of trials: one trial in which they will devote 80% of their attention to task A and 20% of attention to task B, one with 20% on task A and 80% on task B, and one with 50% of their attention on each task. Each priority trial will last about 1 min and will be repeated twice in random order. The *Recall you* activity will be embedded into the physical exercises to train prospective memory [51] (Fig. 1f). On every 3 to 4 sessions, the *Exercises* activity will start with an instruction asking participants to complete a casual task (e.g., to get and drink a glass of water or to open a window, etc.) after a certain amount of time in the physical training. A timer will appear on the top left corner so that participants can track time while doing their exercises. For safety reasons, participants will be instructed to complete the exercise they are engaged in before performing the cognitive task.

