**Fig. 3 Fig3:**
[figure not shown]
Illustration of the different activities of the active control training programme

The physical exercise activity (*Exercises*) will be a computerised version of Helsana’s physical training programme (Fig. 3b). Helsana, a Swiss health insurance company, offers this programme in a booklet. The computerised version will include advice and tips to stay physically active (e.g., to go shopping by foot) and 12 exercises to train upper and lower extremity strength, mobility and balance. It will also provide information about which exercises to choose, the training frequency and precautionary measures to follow. This programme has been judged close to “standard care”, as it is similar to a large range of programmes and recommendations available to the general public. It will differ from the *Exercise* activity available on the StayFitLonger programme, as it only contains a limited number of exercises and does not benefit from interactive content (e.g., videos of exercises), self-management, personalization features, and rewards from the virtual coach.

The four cognitive activities provided in the active control programme will be commercially available leisure activities that do not target specific cognitive processes and do not teach cognitive strategies [52–56]. The *Crosswords* activity will include 219 puzzles with five different sizes (Fig. 3c). The *Sudoku* activity will include around 5000 puzzles with four levels of difficulty (Fig. 3d). The *Attention!* activity will be a maze arcade game inspired from Pac-Man in which participants eat dots in a maze while trying to avoid coloured ghosts (Fig. 3e). The *Countdown* activity will be embedded into the *Exercises* activity and triggered randomly every 3 to 4 days. It will require that participants count backward from 100 to 1 or recite the alphabet from Z to A while doing their exercise.

There will be no chat room, psycho-educational content or virtual coach included in the active control training programme.

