#### Variables

*Adherence.* For the entire duration of the study (between T0 and T1, and T1 and T2), three measures of adherence in relation to the device usage will be recorded directly from the application (Table 3): dose measured by the time (min) spent on the programme per week; volume corresponding to the total number of repetitions performed per week within each activity (e.g., 3 quizzes completed while using the Quiz activity); and frequency corresponding to the number of sessions per week. These will be recorded separately for the physical and cognitive activities. Adherence will be calculated for each individual by plotting weekly data over the entire training period.

**Table 3 Tab3:** List of variables measured during the adherence sub-study

Adherence sub-study variables		Timepoints		
***Domain***	***Variable***	T0	T1	T2
Adherence	Dose variable: total time of training for each activity	During training		
	Volume variable: number of times each activity is carried out			
	Frequency variable: number of training sessions of at least 30 min performed per month			
User experience	Ad-hoc questionnaire exploring the quality of the introductory course	X		
	AttrakDiff 2 scale		X	X
Acceptability	Ad-hoc questionnaire to obtain ratings on different components (enjoyment, appropriateness, safety, self-evaluation)		X	X
Usability	Ad-hoc questionnaire exploring the impact of unique features of the programme (virtual coach, social interactions, preference, gamification, educative content, self-management, usability)			X

*User experience.* The AttrakDiff 2 scale [78] will evaluate user experience (Table 3) with a 28-item questionnaire given at T1 and T2. It will measure attractiveness, pragmatic quality and hedonic qualities (stimulation and identity) of the application. Pragmatic quality corresponds to usability for instance efficiency, effectiveness and learnability. Hedonic qualities refer to the programme’s originality and beauty. In addition, a 9-item questionnaire will be given at T0 to ask participants’ knowledge regarding the effects of cognitive and physical interventions and the quality of the introductory courses.

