#### Statistical analyses

Dose, frequency and volume variables will be analysed with polynomial regression models including linear and non-linear trajectories. This will allow to establish the best fitting model describing the use of the programme over time. Regression analyses will examine whether the cumulative values on adherence variables are predicted by personal characteristics, and the group to which they were assigned. We will also examine adherence dichotomously by classifying participants as a function of whether they maintain or not the recommended dose of the programme over time. Finally, we will evaluate whether change scores on primary and secondary measures of efficacy are correlated with adherence.

Qualitative analyses will be used to characterize usability, acceptability and user experience. In addition, correlations analyses between these parameters and a series of variables (age, sex, education, cognitive profile, participant’s technology and gaming profile) will be performed.

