We are aware of the potential limitations associated with this study. First, the StayFitLonger study spans over a full year and it is hard to predict whether participants will commit for such an extended period of time. Note, however, that we rely on a two-part design, with the RCT portion only lasting 26 weeks, and that attrition will be examined separately for the two portions. Second, while the use of feedback and rewards in the programme was meant to boost motivation, the frequency at which they appear has been set as a fixed parameter to avoid a bias between participants. Hence, this aspect was not personalized. In order to take into account that some participants may dislike receiving regular feedback, they will be able to deactivate this feature during the adherence sub-study. Adherence will be measured from the tablet application, but it is possible that some participants, intentionally or not, start an activity and let the application run in the background while they are actually not doing the activity. To counteract this possibility, the StayFitLonger programme includes a function that stops the application after 10 min of inactivity. However, it has not been implemented in the active control programme. This will be monitored as carefully as possible during data analysis to assess possible outliers in the time of use data of the active control group.

In conclusion, the StayFitLonger study will examine the efficacy, adherence and perception of a home-based computerised multi-modal training programme in robust and pre-frail older adults. Positive results on the StayFitLonger study will pave the way to further development and commercialisation of a scientifically grounded and empirically validated application which will improve the physical and cognitive health associated with independent life at home.

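### The unqualified analyst blind is not reconciled with a usage-outlier check of the control arm only, or with activity-level usage data from which the arm can be inferred

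*Protocol article*

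**What the plan says.** Under Efficacy trial, Randomisation and blinding procedure, the article says "Research team members responsible for the statistical analyses will be blind to the training conditions". The sentence is not restricted to particular analyses or to a period.

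The limitations part of the Discussion explains that the StayFitLonger application closes after 10 minutes of inactivity and that the control application does not. Recorded time in the control arm may therefore include idle time. The remedy offered is careful monitoring "during data analysis to assess possible outliers in the time of use data of the active control group".

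Under Adherence sub-study, Variables, volume is counted within each activity, with the example "e.g., 3 quizzes completed while using the Quiz activity". Table 3 also describes time of use by activity. Recording covers T0 to T1 as well as T1 to T2.

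Under Adherence sub-study, Statistical analyses, assigned group is a predictor of cumulative adherence, and "we will evaluate whether change scores on primary and secondary measures of efficacy are correlated with adherence". The Abstract lists adherence among the moderators of efficacy.

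Under Procedure and data management, access is restricted by type of data, with assessors as the example, and "data collected directly by the programme will be transmitted and maintained in a secured server", apart from the REDCap database.

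**The concern.** An outlier check directed at one named arm cannot be made by a person who does not know the arms. The article places this check within data analysis and does not give it to anyone outside the team it has just called blind. Anyone who works with the T0 to T1 activity records could also work out the arm from what was played.

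Two things are at stake. The first is accuracy of reporting: a paper that repeats the blinding sentence would claim a blind for analyses that do not have one. The second is judgement. The time-of-use data are measured differently in the two arms, so decisions about extreme values matter. As planned, those decisions would be made for one arm only, by someone who knows which arm it is, with no stated rule. The results feed the comparison of adherence between arms and the analyses that relate adherence to change in efficacy outcomes.

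**Working it through.** The document gives no figure to reproduce, so the main check compares statements.

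1. **Does the control-only check need the arm?** Yes. Regression on assigned group, or a contrast with control as reference, can be run on a masked code. A check of the active control group cannot, because the reason for it (no inactivity stop) belongs to that arm alone.

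2. **Do usage data reveal the arm?** From the sections on the two programmes:

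| Programme | Cognitive activities | Found in this arm only |
|---|---|---|
| StayFitLonger | Quiz, 4 Images/1 Word, Attention!, Recall you | Quiz, 4 Images/1 Word, Recall you |
| Active control | Crosswords, Sudoku, Attention!, Countdown | Crosswords, Sudoku, Countdown |

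Only the labels Exercises and Attention! are shared. Three of four cognitive activities per arm are specific to it, so an unrecoded T0 to T1 record of any of these identifies the arm. Totals of physical and cognitive minutes would not carry this cue. After T1 everyone in the sub-study uses StayFitLonger, so later records alone do not separate the groups.

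3. **Do usage data meet the efficacy outcomes?** Yes, in the correlation of change scores with adherence and in adherence as a moderator.

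4. **Does the primary analysis need usage data?** No. Under Analysis of efficacy on primary and secondary outcomes, the mixed model has Intervention, Time (T0, T1) and their interaction as fixed effects. It can be fitted on codes A and B.

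**Illustration, for choosing the fix only.** Assume identical lognormal usage in both arms (log-scale SD 0.4 to 0.8), 36 to 48 participants per arm (36 is the robust recruitment target per group; about 96 / 2 = 48 are in the adherence sub-study), and a two-sided Welch test at 5%, with 6,000 simulated trials per setting. Deletion is an assumed step; the article speaks only of assessing outliers.

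| Handling of high values | False-positive rate for the usage comparison |
|---|---|
| None | about 5% |
| Delete control values above the control mean + 2 SD | about 10 to 16% |
| Delete in each arm above its own mean + 2 SD | about 9 to 11% |
| One common cap applied to both arms | about 5% |

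One-arm deletion also lowers the control mean by about 5 to 15%. These rates concern the comparison of usage between arms, not Timed-Up & Go or any other efficacy outcome.

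**The case against.** The strongest reply is that the blinding sentence belongs to the efficacy trial, while the adherence sub-study has its own design and analysis sections. The Discussion sentence is passive and names nobody, so an unblinded data manager could make the check. Coordinators and instructors are unblinded already. Usage data sit on a separate server, and access is restricted by data type. Looking harder at the arm without the inactivity stop is a reasonable response to a disclosed difference in measurement. Order of analysis and numerical outlier rules commonly belong in a statistical analysis plan, which is not shown.

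Most of this stands, and it excludes several stronger readings. A reader might infer that the logs name the arm. The article does not say so: the arm can be inferred from activity labels, and recoding or totals could hide it. A reader might infer that the blinded analysts are themselves told to screen the controls. No one is assigned. A reader might infer that control outliers will be removed. The article says only that they will be assessed. A reader might infer that a blind primary analysis is impossible. It is not, because that model needs no usage data. The absence of a stated order, analysis set or scoring rule is not a fault of an article.

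What the reply does not remove is the conflict between two current statements: an analyst blind without exception, and a step within data analysis that requires knowledge of the arm. The access restriction does not settle it, since its one example concerns assessors and it does not mention analysts. Nor is the sub-study wholly separate, because adherence returns as a correlate and moderator of efficacy.

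**Conclusion.** The point holds in a limited form. As worded, the analyst blind does not extend to all planned analyses, and the check for usage outliers covers one arm only. The parts exposed are the between-arm comparison of adherence and the analyses that join adherence to efficacy change. No bias in the Timed-Up & Go result, or in the secondary mixed models, is shown.

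The size cannot be fixed from the document. The 10 to 16% error rate rests on deletion, a mean + 2 SD cut and equal lognormal use, none of which the article states, and it applies to usage alone. Its only role here is to show that repeating the same deletion separately in each arm would not be a sound replacement. The conclusion about inference of the arm assumes that analysts would receive activity-level records without recoding. This is a clarification worth making before analysis, not a threat to the trial's main conclusion.

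**What to change.** 1. In Randomisation and blinding procedure, limit the statement to the primary and secondary efficacy models. Say that these are completed on masked arm codes before activity-level usage files are released to the same analysts. Alternatively, assign usage cleaning to a role outside the blinded team, which then hands over data without activity labels.

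2. In the adherence sub-study's Statistical analyses section, state that the adherence and adherence-efficacy analyses are not blind, unless they use only recoded or totalled usage data.

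3. In the Discussion, replace the control-only check by one prespecified rule applied by code to both arms: a common cap on recorded time of use or, if the logs hold the necessary time stamps, a common limit on idle time. Avoid deletion at each arm's own mean + 2 SD. A cap on total time curbs extreme values but does not remove moderate idle time from the control arm, so the difference in measurement should still be reported as a limitation.

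4. Do not attach an error rate to the present plan. If the simulated figures are cited, label them as an illustration that assumes deletion and concerns usage only.

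The cost is a few sentences and some sequencing. The usage data are already stored separately. The downside is a short delay to the adherence analyses.

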#### Interventions

##### Introductory courses

Four face-to-face introductory sessions will be provided to familiarise participants with the material and the assigned application (Table 1). Two sessions of 3 h will present how to use the tablet and accessories (e.g., handling, charging), how to navigate in the application and how to complete the cognitive exercises. Two sessions of 2 h will present the physical exercises and teach participants how to place the motion sensor (Physilog®5, GaitUp, Switzerland) that will be used to record bodily measurements. In both programmes, physical activity instructors will ask participants to practice physical exercises for a total of 30 to 45 min distributed over the day. They will be recommended to train using the same physical exercises for at least 3 weeks with three sessions per week and a day of rest between each session. Cognitive training instructors will encourage participants to practice the cognitive exercises at least 3 times per week for 15 min each time. Participants will be made aware that during an ideal training session, activity should be perceived as of moderate difficulty. Instructions on physical and cognitive activities will be provided by a different instructor, the same for both programmes. Instructors will specifically be asked to present and explain the two programmes in similar ways.

